### Feasibility

Our medical oncologist ([name]) typically sees 45 to 50 new glioblastoma patients each year, and roughly half of these patients live outside of Halifax. To increase our reach, we have partnered with [name] (Acadia University, Wolfville) to accommodate patients within the Western zone who may not be able or willing to travel to the main Halifax site. Anticipating a 60%-65% accrual rate, a sample of 12 patients to 13 patients per year is deemed feasible. Should participant accrual be more challenging than anticipated, we will open recruitment to grade III gliomas.

### Statistical Analyses

Descriptive statistics will be used to describe the population, accrual, program adherence, and safety. Study outcome measures will be assessed pre- and postintervention and will be analyzed using an intention-to-treat approach. A multiple imputation model will be used to account for any missing data. All participants will then be entered into a mixed effects model with participant group assignment at randomization and time point (pre- and posttest) as fixed factors and participant entered as a random factor. Due to feasibility in recruiting participants in the allotted time, the study will not be fully powered to detect sex-based differences; however, effect sizes associated with the intervention will be calculated and presented for each sex.

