**Objective:**

The primary purpose of this study is to establish whether an individualized circuit-based program will reduce steroid-induced muscle myopathy, as indicated by maintained or improved functional fitness for patients on active treatment and receiving steroids.

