### Study Design and Procedures

This manuscript has been written in accordance with the Standard Protocol Items for Randomized Trials (SPIRIT) 2013 guidelines [49]. This is a 2-armed, randomized controlled trial with repeated measures. Eligible participants will be referred to our exercise lab located at the Nova Scotia Cancer Center, Halifax, Nova Scotia, Canada. Here, they will provide informed consent, complete a baseline survey, and undergo a comprehensive functional fitness assessment conducted by a clinical exercise physiologist (CEP). Following baseline assessments, participants will be randomized 1:1 to either the 12-week exercise intervention (EX) or standard of care, waitlist control group (CON). Block randomization in groups of 4 will be used to ensure an equal balance of participants in each group throughout the study period. The allocation sequence will be concealed from the project coordinator who will be involved in assigning patients to groups. Given the nature of the exercise-based intervention, it not possible to blind participants or the CEPs to group allocation. All participants will return to the exercise lab at the end of the 12-week study to complete a final assessment (Figure 1).

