### Sample Size

Sample size is based on a meaningful change (effect size 0.30) in physical performance [75]. A sample of 24 (12 per group) will allow us to detect differences as small as 0.3 points to 0.8 points on the SPPB with 80% power based on an ɑ=.05 with no sphericity correction. Although randomization should account for variations in sex, we will strive to enroll 38 participants (see the Feasibility section) to explore this covariate.

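### The outcome model lists only group and time as fixed factors and names no treatment contrast; read as main effects, its group coefficient estimates half the effect

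*Protocol article*

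**What the plan says.** All of the following is in the protocol article.

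- **Model (Statistical Analyses).** The fixed and random terms are "participant group assignment at randomization and time point (pre- and posttest) as fixed factors and participant entered as a random factor". The section mentions no interaction, no baseline covariate and no coefficient or contrast that is to be read as the intervention effect.
- **Occasions (Statistical Analyses).** "Study outcome measures will be assessed pre- and postintervention and will be analyzed using an intention-to-treat approach". The pre-test score therefore enters the model as an outcome.
- **Missing data (Statistical Analyses).** "A multiple imputation model will be used to account for any missing data". This comes before the model, so each participant has both values when it is fitted.
- **Order of events (Study Design and Procedures).** Baseline assessment comes first and 1:1 randomisation follows it.
- **Sample size (Sample Size).** "Sample size is based on a meaningful change (effect size 0.30) in physical performance". The number needed and the detectable difference are then given: "A sample of 24 (12 per group) will allow us to detect differences as small as 0.3 points to 0.8 points on the SPPB". Alpha is .05, the power is set at 80%, and sphericity is not corrected for. The recruitment target is 38.

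**The concern.** Randomisation follows baseline, so the expected difference between the arms at pre-test is zero and the whole effect lies in the post-test difference. A model with main effects of group and time has no parameter for that. Its group term averages the arms' differences over the two occasions, and its time term averages the changes over the two arms.

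An analyst who fits the listed terms and reports the group coefficient would halve the effect and give up much of the power. An analyst who reads the list as a factorial design would report a different quantity. The article does not say which is meant, so the primary result depends on a choice that the text leaves open.

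**Working it through.** **Inputs.** From the article: two occasions, balanced after imputation; baseline before randomisation; effect size 0.30; N=24 (12 per arm); 80% power; alpha .05; target 38. Assumed, because not stated: 0.30 is Cohen's f; the pre-post correlation rho is 0.5, with 0.3 and 0.7 also shown; the test is two-sided; the SD is the same at both occasions and set to 1. No SD for the SPPB is given, so results are in SD units.

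**1. The plan's own figure.** For a repeated-measures F test with two groups and m=2 occasions, the group-by-time test has noncentrality f²Nm/(1−rho) on 1 and N−2 df.

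- N=24: 0.09 × 24 × 2 / 0.5 = 8.64, power 0.802. N=22 gives 0.763. So 24 is reproduced.
- The within-participant (time) test has the same noncentrality and df, so it also gives 24.
- The group main-effect test has noncentrality f²Nm/(1+rho): 0.09 × 24 × 2 / 1.5 = 2.88, power 0.368. It would need N=68.
- The match depends on rho: at 0.3 or 0.7 the interaction calculation gives 34 or 16.

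**2. What each term estimates.** Let delta be the true between-arm difference at 12 weeks and c the control arm's change.

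- Group coefficient, main effects only: (0 + delta)/2 = delta/2.
- Time coefficient, main effects only: (c + c + delta)/2 = c + delta/2.
- Group-by-time coefficient: delta.
- Baseline-adjusted 12-week difference: delta.

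The halving holds at any rho; chance imbalance at baseline adds noise around it. In 300 simulated trials (19 per arm, rho 0.5, delta 1.0) the mean group coefficient was 0.461 (SE 0.016). This equals the simulated chance baseline difference plus half the interaction estimate: −0.035 + 0.993/2 = 0.461. The interaction averaged 0.993 and the baseline-adjusted difference 0.974.

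**3. Precision.** With n per arm the variances are (1+rho)/n for the group coefficient, 4(1−rho)/n for group-by-time and 2(1−rho²)/n for the baseline-adjusted difference. The last divided by the second is (1+rho)/2, which is 0.75 at rho 0.5: a variance 25% lower.

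**4. Power.** For the interaction, f = 0.30 implies a difference in change of 4f = 1.2 SD. At n=12 and rho 0.5:

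- Group coefficient: SE √(1.5/12) = 0.354; 0.6/0.354 = 1.70.
- Group-by-time: SE √(2/12) = 0.408; 1.2/0.408 = 2.94.
- Baseline-adjusted: SE √(1.5/12) = 0.354; 1.2/0.354 = 3.39.

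Noncentral t power, with N−2 df for the first two and N−3 for the third, effect held at 1.2 SD:

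| N | rho | Group coefficient | Group-by-time | Baseline-adjusted |
|---|---|---|---|---|
| 24 | 0.3 | 41% | 66% | 84% |
| 24 | 0.5 | 37% | 80% | 90% |
| 24 | 0.7 | 33% | 95% | 97.5% |
| 38 | 0.3 | 61% | 86% | 96.5% |
| 38 | 0.5 | 55% | 95% | 99% |
| 38 | 0.7 | 50% | 99.6% | 99.9% |

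The baseline-adjusted column is analytic. Simulation at N=24 and rho 0.5 gave 88% to 89%.

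**The case against.** The strongest reply is that the article lists factors, not coefficients. Naming the factors of a two-group, two-occasion design is common shorthand for the factorial model, the article calls the trial a randomised design with repeated measures, and it condenses a fuller document that is not shown. The sample size also matches a within or interaction test and not a group main effect, which suggests that a contrast in change was in mind. This stands as far as it goes. A reader might infer that the primary analysis is simply biased towards zero by 50%, but the text supports that only if the model is fitted without the interaction and the group coefficient is taken as the effect, and it says neither.

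Three other strong readings also fail.

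- **That N=24 proves an interaction was planned.** The time test gives the same number, and both matches rest on the assumed f and rho.
- **That most of the planned power is lost.** At N=24 more than half goes (37% against 80%), but at the target of 38 the figures are 55% and 95%.
- **That the objective sets a within-arm criterion.** It is worded "as indicated by maintained or improved functional fitness for patients on active treatment and receiving steroids", but the article specifies a concurrent randomised control and intention-to-treat analysis with assigned group in the model, and no within-arm test.

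It can also be said that a group-by-time contrast is valid and that baseline adjustment is optional. Both are true. What remains is that the article does state the model's terms, and none of those listed is the treatment effect.

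**Conclusion.** The point holds in conditional form. As listed, the model has no term that estimates the treatment effect. Fitted with main effects only, its group coefficient has expectation delta/2 whatever the pre-post correlation, given balanced data and baseline before randomisation. The consequence is attenuation and lost power; with no effect the coefficient is centred on zero, so false positives are not the issue. Fitted as a factorial model, the group-by-time contrast is unbiased but has a larger variance than the baseline-adjusted comparison, by a factor of 2/(1+rho), or 1.33 at rho 0.5.

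The power figures rest on reading 0.30 as Cohen's f, on rho = 0.5 and on a 1.2 SD effect, none of which the article states. The halving and the variance ratio do not depend on the effect size.

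**What to change.** In Statistical Analyses, state the treatment effect as the between-arm difference in 12-week SPPB adjusted for baseline SPPB (ANCOVA). An equivalent choice that keeps the mixed model is to include a group-by-time term and constrain the arm means to be equal at baseline; in the simulation above the two averaged 0.974 and 0.975. Report that one contrast with its 95% CI, and use the same form for handgrip strength and the secondary outcomes. If the full factorial model was intended, say so and name the group-by-time contrast as the effect; this removes the ambiguity but not the loss of precision.

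The cost is a sentence or two of text. The baseline score is already collected, and no patients, visits or data are added.

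### Exploring sex is the reason given for enrolling 38 rather than 24, but the only sex output described is a separate effect size per sex, which does not address whether the effect differs by sex

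*Protocol article*

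**What the plan says.** Protocol article, Sample Size: the calculation rests on an effect size of 0.30, and "A sample of 24 (12 per group) will allow us to detect differences" at 80% power and a 5% significance level. The target is then raised for a stated reason: "we will strive to enroll 38 participants (see the Feasibility section) to explore this covariate", the covariate being sex.

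Protocol article, Statistical Analyses: the outcome model is a mixed model with randomized group and time point (pre, post) as fixed factors and participant as a random factor. Sex is not among the factors named. The section concedes that the trial lacks full power for differences between the sexes, and offers in its place that "effect sizes associated with the intervention will be calculated and presented for each sex".

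The article mentions no between-sex contrast, no interaction with sex and no interval for either.

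**The concern.** The sex question is the reason given for 38 - 24 = 14 of the 38 places (14/38 = 37%). The analysis described for it does not match the question. To ask whether sex modifies the effect is to ask about the difference between two intervention effects, and that difference has its own standard error, larger than that of either effect. If the effects are presented side by side, the reader has to form the difference by eye without seeing its uncertainty.

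At this sample size the uncertainty is large. Two sex-specific estimates can lie well apart when the true effect is the same in both sexes, and a reader could take the gap for a finding. The low-power caveat tells the reader to be careful, but it does not supply the estimate and interval that would show how careful to be.

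**Working it through.** **Inputs from the article.** Effect size 0.30; 24 patients (12 per group); 80% power; alpha 0.05; enrolment target 38; two arms allocated 1:1; two time points.

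**Assumptions not in the article.** Pre-post correlation ρ from 0.5 to 0.8; sex split from even to 30:70; equal arms within each sex; all 38 analysed. SD means the outcome SD at a single time point.

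**Step 1: reproduce the stated sample size.** Read 0.30 as Cohen's f in a repeated-measures ANOVA, within-between interaction, with N patients and m = 2 time points. The noncentrality is λ = f²·N·m/(1 − ρ). At N = 24 and ρ = 0.5, λ = 0.09 × 24 × 2/0.5 = 8.64, and power is 80.2%. The stated 24 is reproduced. Other correlations give other sizes (N = 34 at ρ = 0.3, 16 at 0.7, 12 at 0.8). Reading 0.30 as a standardized mean difference would need 175 per arm. A correlation of 0.5 is therefore the value consistent with the article's own figure, and it is the reference case below.

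**Step 2: standard error of the gap between the sexes.** With n_f women and n_m men, each split equally between arms:

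- SD of change = SD × √(2(1 − ρ)), which equals 1 SD at ρ = 0.5.
- SE of the effect in one sex = SD of change × √(4/n).
- SE of the gap = SD of change × √(4/n_f + 4/n_m).
- With no true sex difference, mean absolute gap = SE × √(2/π) = 0.798 × SE.

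Reference case, 19 women and 19 men: SE in each sex = √(4/19) = 0.46 SD; SE of the gap = √(8/19) = 0.65 SD; mean absolute gap = 0.798 × 0.649 = 0.52 SD.

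**Step 3: range over the assumptions (N = 38, no true sex difference).**

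| ρ | Sex split | SE of gap (SD) | Mean absolute gap (SD) | P(gap > 0.5 SD) |
|---|---|---|---|---|
| 0.5 | even | 0.65 | 0.52 | 44% |
| 0.5 | 40:60 | 0.66 | 0.53 | 45% |
| 0.5 | 30:70 | 0.71 | 0.56 | 48% |
| 0.7 | even | 0.50 | 0.40 | 32% |
| 0.8 | even | 0.41 | 0.33 | 22% |
| 0.8 | 30:70 | 0.45 | 0.36 | 26% |

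Adjusting for baseline (ANCOVA) at ρ = 0.5 with an even split gives a mean gap of 0.45 SD, inside this range. If attrition left only 24 analysed, the reference case would rise to 0.65 SD.

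**Step 4: what the direct contrast would deliver.** In the reference case the group-by-time-by-sex estimate has a 95% CI half-width of 1.96 × 0.649 = 1.27 SD (normal), or 1.32 SD using t with 38 − 4 = 34 degrees of freedom. The difference detectable with 80% power is about 1.82 SD. Power for a true sex difference of 0.5 SD is 12%.

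**The case against.** The strongest reply is that this is a condensed article with a caveat already in it. The sentence listing the model terms is plainly abbreviated: it does not name the group-by-time interaction either, which the main comparison needs. A statistical analysis plan that is not shown could contain the sex interaction. The article calls the sex work exploratory, says power is limited and plans no sex-specific test or conclusion. Descriptive effects by sex are not an error in themselves, and the proposed contrast would be too imprecise to settle anything.

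Much of this stands, and it limits what may be claimed.

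- A reader might infer that the trial will never estimate the between-sex difference. The article shows only that it describes no such estimate.
- A reader might infer that chance gaps will be reported as sex effects. The article says nothing of the kind; the risk is that they can be misread that way.
- A reader might count how often one sex would reach significance and the other not. The plan contains no significance rule by sex, so that count would test a rule the plan does not have.
- A reader might fault the remark "Although randomization should account for variations in sex, we will strive to enroll 38 participants" and ask for sex adjustment in the main analysis. Stable sex differences in level cancel in the within-person pre-post contrast, chance imbalance under randomization is not bias, and adjusting in a trial this small is a matter of preference. That remark is no defect here.

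What the reply does not remove is the mismatch. The article does not leave the sex analysis open: it names the output, and presents it as what will be given in view of low power. A difference with a wide interval displays the uncertainty; two separate effect sizes leave it for the reader to work out.

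**Conclusion.** The point holds as a mismatch between a stated purpose and a stated output. Sex is the reason given for 14 of 38 places, and the described output does not address whether the effect differs by sex. With no true difference, the two estimates would be apart by about 0.3 to 0.6 SD on average at N = 38 (0.33 to 0.56 SD in the cases computed; 0.52 SD at the correlation that reproduces the article's 24). The size depends on the assumed correlation, sex split and absence of attrition, and should be quoted as a range. The matter is confined to the exploratory sex analysis; the primary comparison and its inference are unaffected.

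**What to change.** In Statistical Analyses, replace the sentence on effect sizes by sex with a short specification for the exploratory sex analysis:

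- Fit one additional model that adds sex and its interactions with group and time, including group by time by sex.
- Report the group-by-time-by-sex estimate with its 95% CI as the sex result, labelled exploratory.
- Take the sex-specific intervention effects from that same model, each with its CI.

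Keep the caveat on power. The main model need not change.

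The cost is a sentence or two and one secondary model, with no new data or patients. The model uses a few more degrees of freedom. Its interval will be wide (half-width about 1.3 SD at a correlation of 0.5), so the report will show openly that 38 patients do not resolve the sex question.

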## Discussion

### Overview

Glioblastoma is a devastating diagnosis with a high mortality rate and rapid loss of function and independence; thus, it is imperative to consider factors such as symptom management, maintaining functional independence, and preserving or improving QOL for the duration of the patients’ lives. Physical exercise has been well-established to improve functional capacity and QOL in the cancer population. However, few studies have evaluated the efficacy of exercise in mitigating the debilitating physical and functional deficits experienced by glioblastoma patients. Specifically, given the high symptom burden and lack of clinical trials examining the efficacy of exercise in this population, there remains a hesitancy to prescribe any form of exercise. Although the safety and feasibility of exercise for glioblastoma patients have not been widely studied, emerging evidence suggests that brain cancer patients are interested and able to safely engage in physical exercise. Employing a much-needed randomized design, this study will examine the impact of a tailored, circuit-based resistance training program on functional fitness for glioblastoma patients on active treatment. It is anticipated that this study will demonstrate that resistance training not only is safe and feasible for those with glioblastoma but also significantly improves functional status by protecting against steroid-induced myopathy, thereby helping glioblastoma patients maintain their independence, which could lead to marked improvements in QOL.

### Dissemination Plan

The proposed work is supported by a multidisciplinary team with the expertise, experience, and infrastructure to ensure the successful implementation of the study. Building on over 13 years of exercise programming for cancer patients and survivors in Nova Scotia, and with the support of the Nova Scotia Health Cancer Care Program, we have built a strong provincial outreach and patient engagement strategy that has provided the necessary foundation for province-wide implementation and dissemination.

Our knowledge translation plan will be directed by 2 main objectives: (1) to raise awareness and understanding of the benefits of physical activity or exercise for glioblastoma patients and their families and (2) to advance the field of study. To address our first objective, following the conclusion of the study, we will create and promote a webinar to share lessons learned with glioblastoma patients and their families. We will also summarize the study findings in a lay document that will be posted on our website [78]. To address objective 2, we will publish our findings in peer-reviewed publications and will present our findings at local, national, and international conferences.

### Conclusions

In brief, this study will play a critical role in better understanding how physical exercise can foster an optimal level of function, independence, and QOL in glioblastoma patients.

## Appendix

Multimedia Appendix 1 Grant agency peer review - reviewer 1.

Multimedia Appendix 2 Grant agency peer review - reviewer 2.

Multimedia Appendix 3 Grant agency peer review - reviewer 3.

## Abbreviations

6MWT: 6-minute walk test
CEP: clinical exercise physiologist
CON: waitlist control group
CTCAE: Common Toxicity Criteria Adverse Event
DEX: dexamethasone
EX: exercise group
FACIT-F: Functional Assessment of Chronic Illness Therapy-Fatigue
FACT-Br: Functional Assessment of Cancer Therapy-Brain
GLTEQ: Godin Leisure-Time Exercise Questionnaire
KPS: Karnofsky Performance Status
MRI: magnetic resonance imaging
QOL: quality of life
SPIRIT: Standard Protocol Items for Randomized Trials
SPPB: Short Physical Performance Battery
